#### Incremental analysis

We will estimate the differential costs and QALYs predicted by the model and—where relevant—calculate the incremental cost-effectiveness ratio (ICER), defined as the ratio between the mean difference in costs and the mean difference in QALYs. As decision makers need to assess whether an intervention is ‘value for money’, we will compare the ICER against two ‘thresholds’: one ranging between £20 000 and £30 000 per QALY gained to mimic the criterion used by NICE for its policy decisions, and another recently proposed by Lomas *et al* who estimated this threshold to be between £5000 and £15 000.^40^

#### Subgroup analysis

In order to reflect variation between individuals in terms of their health benefit, resource use and costs, we will run the Markov state transition model for a series of different patient profiles. This will enable us to reflect the impact that patient characteristics may have on the value for money assessment of I-WOTCH. The rationale for this approach stems from the recognition that the baseline risk (and possibly the treatment effect) may vary between individuals based on their opioid use, pain severity and pain conditions. The trial’s predefined subgroups based on baseline variables are as follows: (1) pain severity score (5–8, 9–11 and 12–15); (2) opioid usage in MED (0–20 mg, 30–59 mg, 60–89 mg, 90–119 mg, 120–149 mg and >=150 mg); (3) pain conditions (fibromyalgia, musculoskeletal, arthritis, back pain, neurological, cancer and other) and (4) duration of opioid intake (less than 1 year, 1–5 years and more than 5 years).

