## Methods

### Study details (population, setting, location, intervention and comparator)

A detailed study protocol for the I-WOTCH trial has been reported in a separate manuscript.^19^ Briefly, I-WOTCH is a multisite, patient-centred, open RCT enrolling adult patients with non-malignant chronic pain in England. The trial’s target sample size is 542 participants, individually randomised (1:1) to receive the I-WOTCH intervention or best usual care. The I-WOTCH intervention is an 8–10 weeks’ course—consisting of a mixture of group sessions led by two trained I-WOTCH facilitators, two one-to-one individual sessions and two telephone consultations with the I-WOTCH-trained nurse facilitator—adjunct to best usual care. Best usual care consists of general practitioner (GP) care with relaxation package and a booklet called ‘My Opioid Manager’.

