#### Cost of medication

Unit costs of the medications (table 1) will be obtained from the British National Formulary (BNF).^32^ For each strength and preparation of a given pain killer drug, we will extract the cost per pack (or bottle) from the BNF and we will calculate the relevant morphine equivalent dose (MED) using the same algorithm used in the I-WOTCH clinical analysis. This is being updated from that used to estimate MED for stratification at the time of randomisation. For each opioid-based medication reported to have been used by individuals in the I-WOTCH study, we will estimate their unit cost per MED and use it to estimate a weighted average cost per MED over all opioid medications used in the trial.

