#### Modelling

A Markov state-transition model was developed to facilitate the estimation of the long-term mean costs and QALYs associated with the I-WOTCH intervention and usual care. The initial conceptual structure of the model was informed by a systematic analysis of the components of the I-WOTCH intervention. This task was supported and enhanced by critically appraising published decision models that evaluated the use of opioids in chronic non-malignant pain. The face validity of the model structure was further refined by holding a series of meetings with the project team involving clinical experts from the I-WOTCH study. This process is described in detail in a separate related manuscript currently in preparation.

Figure 1 depicts a schematic representation of our final model structure, which is organised around five key states (ie, represented as ovals in figure 1). At any time period, patients can be in one of the following mutually exclusive states: (a) long-term opioid therapy (LTOT)—representing individuals candidate for the intervention, who have been using strong opioids for more than 3 months; (b) I-WOTCH tapering (IT)—individuals committed to tapering as part of the I-WOTCH intervention; (c) patient-driven tapering (PT)—individuals self-committed to tapering without the intervention; (d) successful opioid-less management of pain (SOLMP)—individuals completed withdrawal from opioid use; and (e) dead (D).

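### The predefined opioid-dose subgroups skip from 20 to 30 mg MED, so a baseline dose between those values belongs to no dose subgroup

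*Protocol article*

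**What the plan says.** The Subgroup analysis section of the protocol article introduces its list with "The trial’s predefined subgroups based on baseline variables are as follows". The second item is "opioid usage in MED (0–20 mg, 30–59 mg, 60–89 mg, 90–119 mg, 120–149 mg and >=150 mg". The first item, in the same sentence, is "pain severity score (5–8, 9–11 and 12–15".

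The purpose is given just before the list: "we will run the Markov state transition model for a series of different patient profiles", so that variation in baseline risk, and possibly in treatment effect, by opioid use, pain severity and pain condition can be reflected in the value-for-money results.

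Two other places bear on the point. The Modelling section describes the long-term opioid therapy state as people "who have been using strong opioids for more than 3 months" and gives no dose range. The Cost of medication section says of the algorithm for calculating MED: "This is being updated from that used to estimate MED for stratification at the time of randomisation".

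**The concern.** A set of dose bands used to define subgroups should place every patient in exactly one band. Here there is a hole between the first and second bands, and nothing in the article says where a patient with, for example, 25 mg MED at baseline should go.

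Two outcomes are possible if the text is followed. Either those patients are silently left out of every MED subgroup, or an analyst has to choose a band for them when the data are already in hand. The second would weaken the claim that the subgroups were predefined. The patients concerned are at the low end of the dose range, so the lowest-dose subgroup is the one whose membership is most in doubt.

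The written cut-points could matter more than usual because the MED algorithm is being revised after randomisation. If baseline MED is recalculated for the subgroup analysis, a patient's stratum at randomisation cannot simply be carried over, and the printed bounds would have to do the work. The article does not say whether baseline MED will be recalculated for this purpose, so this is a conditional point.

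**Working it through.** **Inputs.** The six MED bands and the three pain severity bands, all from the Subgroup analysis section of the protocol article. No sample size or power formula applies; the check is whether the bands cover the dose range.

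**Formulas.** Step between bands = lower bound of the next band − upper bound of this band. Whole-mg values in a closed band = upper bound − lower bound + 1.

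| Band (mg MED) | Whole-mg values | Step to next band (mg) |
|---|---|---|
| 0–20 | 20 − 0 + 1 = 21 | 30 − 20 = 10 |
| 30–59 | 59 − 30 + 1 = 30 | 60 − 59 = 1 |
| 60–89 | 89 − 60 + 1 = 30 | 90 − 89 = 1 |
| 90–119 | 119 − 90 + 1 = 30 | 120 − 119 = 1 |
| 120–149 | 149 − 120 + 1 = 30 | 150 − 149 = 1 |
| 150 and above | open | none |

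**Uncovered doses.** Testing every whole-mg dose from 0 to 300 against the bands leaves 21, 22, 23, 24, 25, 26, 27, 28 and 29 mg unassigned: 29 − 21 + 1 = 9 values. Doses of exactly 20 and exactly 30 mg are covered.

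**Comparison within the same sentence.** The pain severity bands have steps of 9 − 8 = 1 and 12 − 11 = 1, and no score from 5 to 15 is left out. The gap is peculiar to the first MED boundary.

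**If the first band ended at 29 mg** (an assumption drawn from the pattern of the other bands), it would hold 29 − 0 + 1 = 30 whole-mg values like the other closed bands, every step would be 1 mg, and no whole-mg dose from 0 to 300 would be unassigned.

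**Could the gap be a deliberate exclusion?** The article states no dose limit that removes patients between 20 and 30 mg. A minimum dose for entry could not produce this pattern either, because the band below the gap is kept.

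**What cannot be computed.** The article gives the target sample size of 542 but no distribution of baseline dose. The nine values are a count of doses, not of patients, and say nothing about how many participants are affected.

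**The case against.** The strongest reply is that this is a one-digit misprint, 20 for 29, in an article that relays definitions set elsewhere. The detailed trial protocol is published separately, MED was already banded for stratification, and the regular 30 mg spacing makes the intended reading easy to guess. Much of this is fair: a misprint is the likeliest explanation, and the article cannot show that the analysis as actually programmed has a gap. What stands is that the article chose to state the cut-points, calls them predefined, and gives no other passage from which the right bound can be recovered. If a correct version exists elsewhere, two public documents disagree.

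A reader might also infer more than the text supports, in four ways:

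- **That these patients have no model profile at all.** The section says the model will be run for a series of profiles; it does not limit the profiles to the listed bands. The Statistical analysis section names opioid use as a regression predictor without saying whether it is categorical. If it is continuous, a profile can be set at any dose. The loss extends to profiles or regressions only where these bands are used as categories.
- **That the main results are biased.** The Analysis section uses individual patient data by intention to treat. The whole-population costs, outcomes and ICER do not depend on the bands unless MED enters the underlying regressions as these categories.
- **That 0–29 mg is established as the intended first band.** It is an inference from the pattern, and the trial's own definition has to confirm it.
- **That the pain-condition list shows the same kind of error.** It reads "pain conditions (fibromyalgia, musculoskeletal, arthritis, back pain, neurological, cancer and other", although the trial enrols "adult patients with non-malignant chronic pain in England". The cancer label could denote a past or coexisting condition in someone whose pain is non-malignant. It deserves a word of clarification, but it is a separate minor matter and adds no weight to the dose gap.

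**Conclusion.** The error is real and exact. As printed, baseline doses above 20 and below 30 mg MED fall in no predefined dose subgroup, and coding the bands literally removes those patients from the MED subgroup analysis. The same holds for any profile or regression that takes the bands as categories.

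Its reach is limited. It concerns a subgroup definition, not the whole-population comparison, which is affected only if MED is coded categorically from these bands. The number of patients cannot be stated without the dose distribution.

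The conclusion rests on the printed bounds alone. The view that the first band was meant to end at 29 mg is an assumption from the 30 mg spacing. Because this is a wrong cut-point in an analysis definition, and not a slip in background text, it should be corrected before the analysis begins.

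**What to change.** First, check the bands against the trial's predefined subgroup definition and the bands used for stratification at randomisation. Then state one contiguous set before analysis. If those sources agree with the 30 mg pattern, the bands would be <30, 30 to <60, 60 to <90, 90 to <120, 120 to <150, and 150 mg or more. Half-open bounds also place non-integer MEDs, which a recalculated equivalent dose may produce. It would help to add whether subgroup membership uses the MED recorded for stratification or the value from the updated algorithm.

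The cost is a line or two of text. No data collection or change to the model structure is needed.

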#### Probabilistic sensitivity analyses

Sampling uncertainty in the model will be captured by characterising each model parameter with an appropriate probability distribution. We will derive the parameters to inform these distributions from the variance–covariance matrix obtained from each regression model. Cholesky decomposition of each variance–covariance matrix will be used to make the simulation more efficient. Sampling uncertainty will be propagated through the model using Monte-Carlo simulation in the form of PSA to understand the effect on the predicted mean QALYs and mean costs associated with each treatment arm. These parameters will then be combined and compared against a range of feasible cost-effectiveness thresholds to obtain an estimate of the probability that I-WOTCH is cost-effective. This information will be represented graphically in the form of a cost-effectiveness acceptability curve.^41^ Also, we will perform scenario analyses for the various distributional assumptions made, for example, on the parametric survival distribution and compare the results for different assumptions.

## Discussion

The scale of the opioid crisis in the UK is not as severe as in the USA. However, recently, it has been reported that opiates are a frequent cause of death due to drug poisoning in the UK.^3 42^ To begin reviewing the benefits and risks of opioid medicine, and make recommendations for regulatory action, an expert working group has been formed by the Medicines and Healthcare Products Regulatory Agency.^43^ This protocol describes the first economic evaluation of an adjunct intervention (ie, I-WOTCH) to support opioid tapering in patients with chronic non-malignant pain. Its findings will provide timely and significant results to inform policy recommendations on how best to tackle the opioids epidemic in the UK and manage the complex landscape of opioids-related health (and financial) risks.

A study that tested the effectiveness of an earlier version of I-WOTCH (ie, the COPERS trial/COping with persistent Pain, Effectiveness Research into Self-management) showed sustained benefits on depression and anxiety in people with musculoskeletal chronic pain.^44^ The COPERS intervention was designed based on cognitive behavioural therapy principles. While in the COPERS trial more than 20% of participants used strong opioids, this was not aimed at opioid dose reduction. In contrast, the I-WOTCH intervention was designed to support opioid reduction and improve activities of daily living.

### Strengths

This paper describes the first economic evaluation analysis of a complex intervention to support opioid tapering, which uses data collected alongside the first UK-based RCT. A within-trial CCA will allow estimating relevant model parameters. The long-term impact on costs and health benefits from implementing the I-WOTCH Programme in England will be assessed in a lifetime decision analytic model populated using trial and previously published data. This analysis is based on a robust conceptual model that reflects clinical practice and long-term adverse events associated with both opioid use and opioid withdrawal. This model will enable estimation of I-WOTCH’s cost-effectiveness over a lifetime horizon and real-life subgroup analyses.

### Limitations

Our decision problem and associated model structure are complex. I-WOTCH’s effectiveness in the short and long term is associated to the occurrence/absence of several interlinked events that determine individual’s transition from one health state to the other. I-WOTCH’s 12-month trial follow-up period is unlikely to allow to capture all events of interest in the long term. This may limit our ability to estimate all relevant transition probabilities on trial-based IPD. A number of model parameters may need to be estimated from published sources and experts’ opinion. Data availability may limit the successful evaluation of the CEA model.

## Ethics and dissemination

The study was approved by the Yorkshire & The Humber—South Yorkshire Research Ethics Committee (16/YH/0325). Appropriate local approvals were sought for each area in which recruitment was undertaken. The current protocol version is 1.7 date 31 July 2019. To inform all health technology assessment stakeholders, our results will be published in peer reviewed journals and presented at scientific conferences. Similarly, I-WOTCH’s newsletter and lay summaries of our results on the study’s website will be our main vehicles to disseminate our findings to study participants and facilitators.

## Patient and public involvement

The involvement of patient and public in the intervention design, development and delivery is outlined in the I-WOTCH clinical protocol paper.^19^ In brief, two lay advisers with chronic pain withdrawal of opioids and experience of clinical trial research have been recruited to the study. Additionally, prior to receiving funding for the study, meetings were held with volunteers with chronic malignant pain to receive input to the design of the intervention structure, duration of intervention and content to be covered. These meetings contributed also to the design of the study including randomisation, best usual care intervention, recruitment processes, as well as outcome measures.
